## **Schedule**

The study will be commenced directly after receiving the permissions to conduct it, estimated at spring 2016. Approximately 100 pancreatic resections are being performed in Helsinki University Hospital annually, and approximately 50 – 60 of these are estimated to be suitable for the trial. Recruiting period is estimated to take approximately 2 years, after which primary and secondary outcome measures can be analyzed and published. Tertiary outcomes will be analyzed when 1, 5, or 10 years have passed from the recruitment of the last patient. Interrim analysis will be made when half of the patients have been recruiting, meaning at 62 patients. Complication outcomes will be analyzed, and based on these the decision whether it is safe to continue study will be made.

## **Statistical analysis plan**

Non-inferiority will be tested by lower limit the mean difference's 90% confidence interval (equivalent of 95% confidence interval of one-sided test). If the lower limit of CCI's mean difference's 90% confidence interval is under -9, non-inferiority is not met. Of primary and secondary outcomes, CCI and length of stay will be presented as mean (standard deviation) and compared between groups using independent t-test with bootstrapping. Only primary outcome will be assessed using non-inferiority testing, and secondary outcomes will be assessed using superiority approach. Categorical secondary outcome measures are compared using Chi square test. Effect sizes are reported either as mean difference with 95% confidence interval or odd ratios (OR) with 95% confidence interval. All p-values reported are two-sided and for superiority testing. P-value <0.05 was considered statistically significant. Missing data, if any, will be reported. Missing data are omitted from analyses of the particular variable in question and no missing data is imputed. All outcomes will be analyzed using modified intention-to-treat analyses, where all randomized patients in whom the study drug is continued after surgery are included in the analyses. Subgroup analyses are performed using superiority testing for patients undergoing pancreaticoduodenectomy or distal pancreatectomy.

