### **Study patients**

**Inclusion criteria**

- Patient scheduled for pancreatic resection (pancreaticoduodenectomy, distal resection, enucleation, or other resection)

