**Randomization**

Patients will be randomized 1:1 to receive either perioperative pasireotide or cortisone treatment. Randomization will be done computer assisted using randomly variable block size. All patients, who fulfill inclusion criteria and do not meet exclusion criteria, will be randomized and allocated treatment will be commenced before surgery. A piece of paper indicating the allocated group will be put in an opaque envelope (so called safety envelope). The envelopes will be numbered and they are opened in numerical order.

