#### Tertiary outcomes

1. Overall survival, 1, 5, 10y
2. Disease-free survival, 1, 5, 10y
3. Disease-specific survival, 1, 5, 10y

Outcome measures will be analyzed in following subgroups: 1) Patients who have undergone pancreaticoduodenectomy, 2) Patients who have undergone distal resection

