## **References**

Laaninen M, Sand J, Vasama K, Laukkarinen J. Whipplen leikkauksen jälkeisiä komplikaatioita voidaan vähentää hydrokortisonihoidolla. *Randomoitu*

plasebokontrolloitu tutkimus. Suomen Kirurgiyhdistys ry 2015 36;4

Collected parameters

Name

Social security number

Date of birth

Gender (1 = male, 2 = female)

Charlson comorbidity index

Medication

Anticoagulation (0 = no, 1 = yes)

Immunosuppression (0 = no, 1 = yes)

Cortisone (0 = no, 1 = yes)

Date of diagnosis of pancreatic tumor (suspicion) (=computed tomography date)

Preoperative diagnosis (1 = pancreatic cancer, 2 = cholangiocarcinoma, 3 = IPMN, 4 = NET, etc)

Neoadjuvant therapy (0 = no, 1 = gemcitabine, 2 = folfirinox, 4 = chemoradiotherapy, 4 = other)

Randomization group (1 = signifor, 2 = cortisone)

Date of surgery

Type of surgery (1 = whipple, 2 = distal resection, 3 = enucleation, 4 = median pancreatectomy, 4 = exploration, 5 = total pancreatectomy, 6 = other)

Venous resection (0 = no, 1 = portal/SMV, tangential or end-to-end, 2 = porta/SMV,

Arterial resection (0 = no, 1 = yes)

Pancreaticojejunostomytype (1 = Heidelberg, 2 = [name], 3 = other)

Consistency of pancreas (1 = hard, 2 = soft, normal)

Pancreatic duct at operation (1 = small, normal, 2 = dilated)

Pancreatic duct size, computed tomography, mm

Drains (0 = no, 1 = one drain, 2 = two drains)

Was study drug continued after operation (1 = yes, 2 = no, hard pancreas/dilated duct in patient undergoing whipple, 3 = no, no operation, 4 = no, total pancreatectomy)

Complications, 30 days from operation

Pancreatic fistula, ISGPS grade

DGE, ISGPS grade

Postop haemorrhagia, ISGPS grade

First complication, C-D class

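### The unadjusted, unstratified CCI comparison across pooled operations is valid, but it forgoes a modest and cheaply available gain in precision

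*Protocol*

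**What the plan says.** The Inclusion criteria admit all partial resections to one population: "Patient scheduled for pancreatic resection (pancreaticoduodenectomy, distal resection, enucleation, or other resection". On allocation, the Randomization section says "Patients will be randomized 1:1 to receive either perioperative pasireotide or cortisone treatment" and "Randomization will be done computer assisted using randomly variable block size". It names no stratification factor and describes a single series: "The envelopes will be numbered and they are opened in numerical order".

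The Statistical analysis plan section fixes the analysis of the primary outcome. CCI is "compared between groups using independent t-test with bootstrapping", and no covariate is named. Procedure enters only as a subgroup factor: "Subgroup analyses are performed using superiority testing for patients undergoing pancreaticoduodenectomy or distal pancreatectomy".

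The list of collected parameters, printed after the references, includes "Pancreatic duct size, computed tomography, mm" and the Charlson index. It also has a type-of-surgery field. That field's codes include exploration and total pancreatectomy, so it records what was done and not what was planned. The planned operation is nevertheless known before randomisation, because two of the Exclusion criteria depend on it.

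**The concern.** The protocol treats gland texture, duct width and type of operation as relevant to risk. The Background defines high risk by a soft gland or narrow duct. The low-risk exclusions and the intraoperative removals apply to pancreaticoduodenectomy only, and two procedures are singled out for subgroup analysis. None of this enters the allocation or the primary estimate.

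If mean CCI differs by procedure, that variation widens the confidence interval, and a chance difference in case mix between the arms moves the estimated CCI difference. The trial is sized at about 80% power without reserve, so precision available at almost no cost is worth having. The t-test is written into the protocol's own analysis section, so it is a stated choice and not a detail left open.

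**Working it through.** **Inputs from the protocol.** Margin 9 points, SD 20 and 62 per group (Sample size); 90% confidence interval, i.e. one-sided 5% (Statistical analysis plan). Power and true difference are not stated. I infer 80% and zero because they reproduce the stated size.

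**Step 1: reproduce the sample size.** n = 2 × [20 × (1.645 + 0.842) / 9]² = 61.06, rounded up to 62 per group, as stated. With 62 per group, SE = 20 × √(2/62) = 3.59. Power = Φ(9/3.592 − 1.645) = 80.5% by the normal approximation (80.1% with the noncentral t). The 90% half-width is 1.645 × 3.592 = 5.91 points.

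**Step 2: effect of adjustment.** If baseline covariates explain a share R² of CCI variance, the residual SD is 20 × √(1 − R²). No R² is in the documents, so the first column is assumed.

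| R² | Residual SD | Power at 62 per arm | 90% half-width | n per arm for 80% |
|---|---|---|---|---|
| 0 | 20.00 | 80.5% | 5.91 | 62 |
| 2% | 19.80 | 81.2% | 5.85 | 60 |
| 5% | 19.49 | 82.3% | 5.76 | 59 |
| 10% | 18.97 | 84.0% | 5.61 | 55 |
| 20% | 17.89 | 87.6% | 5.29 | 49 |

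**Step 3: which R² procedure alone could supply.** With a share p of pancreaticoduodenectomy and a gap of D points in mean CCI between it and the rest, R² = p(1 − p)D²/400. Both p and D are assumed. At p = 60%:

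- D = 5 gives 0.24 × 25/400 = 1.5%.
- D = 10 gives 0.24 × 100/400 = 6%.
- D = 15 gives 0.24 × 225/400 = 13.5%.
- D = 20 gives 0.24 × 400/400 = 24%.

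Reaching 20% from procedure alone would therefore need a gap of nearly 20 points, about twice the 10 points that the protocol calls clinically relevant.

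**Step 4: chance imbalance without stratification** (simple-randomisation approximation). At p = 60% the between-arm difference in share has SD √(2 × 0.6 × 0.4/62) = 8.8 percentage points. The chance of a difference above 10 percentage points is 2 × [1 − Φ(10/8.8)], about 26%. For p from 50% to 70% it is 22–27%. With D = 10, a 10-percentage-point imbalance shifts the CCI difference by 1 point, and a 1.96-SD imbalance (17.2 percentage points) shifts it by 1.7 points.

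**Step 5: are steps 2 and 4 separate losses?** No. The imbalance in step 4 contributes variance D² × 2p(1 − p)/62 = 100 × 0.48/62 = 0.77. The R² of 6% in step 3 is 6% of the squared SE: 0.06 × 12.90 = 0.77. These are the same quantity, and the unadjusted interval already contains it.

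**Step 6: the cost of missing duct measurements.** The Statistical analysis plan section omits missing data and imputes nothing. If a fraction m of patients lacks a CT duct size and is dropped, the variance changes by the factor (1 − R²)/(1 − m). At R² = 5% and m = 5% this is 0.95/0.95 = 1, so the gain is gone.

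**The case against.** The strongest reply is that nothing here is an error. Under randomisation the unadjusted comparison is valid, the sample size reproduces for exactly that analysis, and any trial sized to 80% has no spare power. Step 5 supports this: random imbalance is already paid for in the interval and does not raise the overall error rate of the non-inferiority test. A reader might infer from the 26% figure that the result is biased or that the 5% error rate is exceeded. The documents do not support that.

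The size of the gain is also assumed throughout. The protocol gives no R², no procedure mix and no CCI by procedure, and does not say which case mix the SD of 20 came from. Planning subgroup analyses does not show that procedures differ in mean CCI.

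CT duct size may be a weak covariate. Markedly dilated ducts are excluded, and dilated ducts are removed intraoperatively, among pancreaticoduodenectomies only. The range is therefore cut in one procedure and not in the others. Stratified balance would also be eroded in part by the removals after randomisation, one of which falls only on pancreaticoduodenectomy.

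All of this stands, and it limits the weight of the point. It does not remove the gain: prespecified adjustment for a variable known before randomisation costs almost nothing. Adjustment also helps in the particular trial that turns out unbalanced. With D = 10 and a 1.96-SD imbalance against cortisone (both assumed), the conditional SD is 3.59 × √0.94 = 3.48 and power becomes Φ((9 − 1.72 − 5.91)/3.48), about 65%. With the same imbalance in cortisone's favour and a true difference of 9, the chance of a false claim is Φ((1.72 − 5.91)/3.48), about 11%. Each direction is reached or exceeded in about 2.5% of trials.

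**Conclusion.** The point holds as a modest loss of efficiency, not as a fault of validity. At assumed R² of 2% to 20%, adjustment would raise power at 62 per arm from about 80.5% to 81–88% and narrow the 90% half-width from 5.91 to between 5.85 and 5.29 points. For procedure alone the lower part of that range is more plausible: a 10-point gap gives about 6%, worth roughly two percentage points of power. These figures rest on the protocol's margin and SD, the inferred 80% power and zero true difference, and R² values that no document supplies.

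Two stronger readings should be avoided. One is that power of 88% is to be expected; that needs an R² of 20%, for which there is no support in the protocol. The other is that the procedure covariate is already on file. The data list holds only the operation performed, which is settled after randomisation and after treatment has begun, and is not a suitable adjustment variable.

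**What to change.** 1. Add one baseline field, completed before the envelope is opened: scheduled procedure, pancreaticoduodenectomy or other. Do not adjust for the operation performed.
2. Define the primary estimate as the mean CCI difference from a linear model with arm and scheduled procedure. Compare its bootstrap 90% confidence interval with the 9-point margin. Keep the unadjusted bootstrapped t-test as a sensitivity analysis.
3. CT duct size may be added as a prespecified baseline covariate only with a simple missing-covariate rule, such as mean imputation plus a missing indicator, so that no patient is dropped. State this as an exception to the no-imputation rule.
4. Optionally, use two numbered envelope series, one per scheduled-procedure group. This is cheap, although the removals after randomisation will partly erode the balance.

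The model must be fixed before outcome data by arm are seen, including at the interim look at 62 patients, so that covariates cannot be chosen on the results. The cost is one extra field, a revised analysis paragraph and slightly more work for the study nurse and the analyst. The sample size and the margin stay as they are.

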## **Hypothesis**

Cortisone is non-inferior to pasireotide in preventing postoperative pancreatic fistula and complications

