**Outcome measures**

Primary outcome

Comprehensive complication index 30 days postoperatively

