#### Secondary outcomes

1. Complications (Clavien-Dindo classification), 30 days
2. Rate and severity of postoperative pancreatic fistula (ISGPS classification), 30 days
3. Rate and severity of delayed gastric emptying (ISGPS classification), 30 days
4. Rate and severity of post-pancreatectomy haemorrhage (ISGPS classification), 30 days
5. Length of hospital stay, days
6. Readmissions, 30 days
7. Number of patients received adjuvant therapy among patients with cancer diagnosis

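### The hypothesis claims non-inferiority for pancreatic fistula as well as complications, but the plan has a margin and a non-inferiority test for CCI only, so the fistula part cannot be confirmed

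*Protocol*

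**What the plan says.** The Hypothesis section of the protocol reads "Cortisone is non-inferior to pasireotide in preventing postoperative pancreatic fistula and complications". The Finnish text says the same.

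The primary outcome is "Comprehensive complication index 30 days postoperatively". Fistula stands second in the list of secondary outcomes: "Rate and severity of postoperative pancreatic fistula (ISGPS classification), 30 days".

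The Sample size section fixes a margin of 9 CCI points, with an SD of 20 and 62 patients per group. No other outcome has a margin.

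The protocol's Statistical analysis plan section sets the kind of test for each outcome:

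- Non-inferiority on CCI is judged by a 90% interval: "Non-inferiority will be tested by lower limit the mean difference's 90% confidence interval (equivalent of 95% confidence interval of one-sided test".
- For the rest: "Only primary outcome will be assessed using non-inferiority testing, and secondary outcomes will be assessed using superiority approach".
- For fistula and the other categorical outcomes: "Categorical secondary outcome measures are compared using Chi square test".
- Effect sizes are mean differences or odds ratios with 95% confidence intervals.

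On subgroups, the outcomes section says "Outcome measures will be analyzed in following subgroups: 1) Patients who have undergone pancreaticoduodenectomy, 2) Patients who have undergone distal resection", and the analysis section adds "Subgroup analyses are performed using superiority testing for patients undergoing pancreaticoduodenectomy or distal pancreatectomy".

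**The concern.** The hypothesis names two targets for non-inferiority, and the analysis serves one. A superiority test can show that the fistula rates differ. If it fails to do so, that does not show that cortisone is no worse by more than a tolerable amount. This is not detail left for a later document, because the protocol itself assigns fistula a type of test that cannot answer the hypothesis.

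The Background section gives the purpose: if efficacy is at the same level, the cheaper drug could take over as standard prevention. It also says that pasireotide was adopted at the site to prevent fistula. A reader will therefore look at the fistula result when deciding on the switch. If that result is a non-significant p-value from a small sample, it may be given weight that it cannot bear.

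The subgroup rule has a related weakness. Separate superiority p-values for pancreaticoduodenectomy and distal resection show neither that cortisone is not worse in a subgroup nor that the effect differs between procedures.

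**Working it through.** **1. The plan's own figure.** Inputs from the protocol: margin 9, SD 20, one-sided 0.05 (the 90% interval). Power is not stated; 80% is inferred because it reproduces the figure. Assuming no true difference:

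n per arm = 2 × 20² × (1.645 + 0.842)² / 9² = 800 × 6.183 / 81 = 61.1, rounded up to 62.

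This matches the stated 62 per group. The trial is sized for CCI and nothing else.

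**2. Can CCI carry the fistula claim?** The list of collected parameters codes fistula as one complication type with its own Clavien-Dindo class, so fistula contributes to CCI. CCI sums the burden of all complications, however. More fistulas in one arm can be offset by fewer or milder complications of other kinds, so non-inferiority on CCI does not imply non-inferiority on fistula.

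**3. How informative is the fistula test?** The documents give no fistula rate, so I assume a pasireotide rate p₁ of 10% to 30% and a cortisone rate p₂ that is 10 points worse. All 62 per arm are taken as analysed, fistula is treated as yes/no, and the test is two-sided at 0.05. With unpooled variance:

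power = Φ( 0.10 / √[(p₁(1−p₁) + p₂(1−p₂)) / 62] − 1.96 )

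Example, 15% v 25%: √[(0.1275 + 0.1875)/62] = 0.0713; 0.10/0.0713 = 1.403; Φ(1.403 − 1.96) = Φ(−0.557) = 28.9%.

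The pooled-variance form gives slightly lower values. The half-width of the 95% interval for the risk difference, at equal rates, is 1.96 × √[2p₁(1−p₁)/62].

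| Assumed pasireotide rate | Power for +10 points, pooled / unpooled | 95% half-width at equal rates | Difference detectable with 80% power (pooled) |
|---|---|---|---|
| 10% | 34.3% / 35.0% | 10.6 points | 20.0 points |
| 15% | 28.3% / 28.9% | 12.6 points | 21.9 points |
| 20% | 24.9% / 25.3% | 14.1 points | 23.2 points |
| 25% | 22.7% / 23.0% | 15.2 points | 24.1 points |
| 30% | 21.3% / 21.6% | 16.1 points | 24.7 points |

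A 10-point worse rate would be non-significant in roughly 65% to 79% of such trials.

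**4. Would a fistula margin rescue it?** With one-sided 0.05, 80% power and equal true rates, n per arm = 6.183 × 2p₁(1−p₁) / margin².

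- Illustrative 10-point margin: 6.183 × 0.18 / 0.01 gives 112 per arm at a 10% rate; 6.183 × 0.42 / 0.01 gives 260 at 30%.
- Illustrative 15-point margin: 50 to 116 per arm over the same range.

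The planned 62 per arm falls short everywhere except with the wider margin at the lowest rates.

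**5. Subgroups.** Subgroup sizes are not given. I assume 25, 31 or 35 per arm, with SD 20. The standard error is 20√(2/n), and superiority power for a 9-point CCI difference is Φ(9/SE − 1.96).

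| n per arm | SE | Power for 9 points | 90% half-width (1.645 × SE) | 95% half-width (1.96 × SE) |
|---|---|---|---|---|
| 25 | 5.66 | 35.6% | 9.3 | 11.1 |
| 31 | 5.08 | 42.5% | 8.4 | 10.0 |
| 35 | 4.78 | 46.9% | 7.9 | 9.4 |

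For an interaction test with 31 per arm in each of two subgroups, SE = √2 × 5.08 = 7.18. The interaction detectable with 80% power is (1.96 + 0.842) × 7.18 = 20.1 CCI points.

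**The case against.** The strongest reply is that this is an ordinary hierarchy: one primary outcome tested for non-inferiority, with secondary outcomes tested for superiority. The protocol says so openly, sizes the trial on CCI alone and lists fistula as secondary. Fistula also feeds the CCI, so it is not wholly outside the non-inferiority test. All of this stands as a description of the analysis. It does not remove the mismatch, because the hypothesis names fistula separately and CCI can hide a shift in it.

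A reader might infer that the plan will treat a non-significant fistula or subgroup p-value as proof of non-inferiority. The protocol does not say this. It confines non-inferiority to the primary outcome, labels its p-values as superiority p-values, and promises effect sizes with 95% intervals, which would show the imprecision. Misreading is a risk, not a rule of the plan.

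A reader might also infer that the subgroup tests contradict the hypothesis. They do not, since no non-inferiority hypothesis is stated for subgroups. The superiority tests there merely fit the trial's question poorly. Nor can it be said that subgroup intervals must be wider than the 9-point margin. That is so for the 95% interval at the sizes shown, but the plan's non-inferiority rule uses a 90% interval, and its half-width is below 9 at 31 and 35 per arm.

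Finally, the fistula rates and subgroup sizes are assumptions. The mismatch between hypothesis and analysis depends on none of them.

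**Conclusion.** The point holds for fistula. The protocol hypothesises non-inferiority on fistula but fixes a margin and a non-inferiority test for CCI only. Followed as written, the plan leaves that part of its hypothesis unanswerable. This rests on the text alone.

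The size of the problem rests on assumed pasireotide fistula rates of 10% to 30% with 62 per arm analysed. Power for a 10-point worse rate is then about 21% to 35%, and only differences of about 20 to 25 points are detectable with 80% power. A non-significant fistula result would say little about whether cortisone can replace pasireotide.

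For the subgroups the conclusion is milder. Separate superiority p-values are a poor tool for this trial's question, but they contradict nothing in the protocol.

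**What to change.** 1. Restrict the confirmatory hypothesis and the conclusion to 30-day CCI, in both language versions.
2. Report fistula as an estimate, either a risk difference or the odds ratio already planned, with its confidence interval.
3. State that p>0.05 on any secondary or subgroup test is not evidence of non-inferiority.
4. For pancreaticoduodenectomy and distal resection, replace the within-subgroup superiority p-values with the CCI difference and its confidence interval, labelled descriptive, plus one treatment-by-procedure interaction test.

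I would not make a new fistula margin the main repair. It would be hard to justify from this document, and the sample would mostly be too small to meet it. The subgroup intervals should likewise not become extra non-inferiority claims.

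The cost is a change of wording and a few analyses, with no added patients or data. The claim becomes more modest, the fistula and subgroup intervals will be wide, and the interaction test will have low power.

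### Chi-square is the only test named for four ordered-grade secondary outcomes; it ignores the ordering, gives no single odds ratio on a full grade table, and costs power

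*Protocol*

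**What the plan says.** The Protocol's list of secondary outcomes opens with four graded ones: "Complications (Clavien-Dindo classification), 30 days"; "Rate and severity of postoperative pancreatic fistula (ISGPS classification), 30 days"; "Rate and severity of delayed gastric emptying (ISGPS classification), 30 days"; and "Rate and severity of post-pancreatectomy haemorrhage (ISGPS classification), 30 days". The list of collected parameters records an ISGPS grade for each of the last three and a Clavien-Dindo class for each of up to six complications per patient. Neither list names a cut-off, and neither says which single Clavien-Dindo class represents a patient with several complications.

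The Statistical analysis plan section then gives one rule for all of them: "Categorical secondary outcome measures are compared using Chi square test". On effect measures it says: "Effect sizes are reported either as mean difference with 95% confidence interval or odd ratios (OR) with 95% confidence interval". On testing: "All p-values reported are two-sided and for superiority testing", with "P-value <0.05 was considered statistically significant". It names no rank test, trend test or ordinal model. Only the CCI is tested for non-inferiority.

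**The concern.** Pearson's chi-square gives the same result however the grades are relabelled. A consistent move towards worse grades is spread over one degree of freedom fewer than there are grades, when a test that uses the order would concentrate it on one.

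The stated effect measure does not fit such a table either: a comparison of two arms over four or more unordered categories has no single odds ratio. So either severity is tested without a matching estimate, or the grades are collapsed at cut-offs the Protocol does not give.

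The Hypothesis section speaks of fistula and complications, but fistula gets only a superiority test. A non-significant result from a weak test is easily misread as reassurance.

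**Working it through.** **Inputs from the Protocol.** 62 patients per arm (Sample size), 1:1 allocation, two-sided 5% for secondary outcomes. The 62 reproduces from the primary-outcome inputs with margin 9, SD 20, one-sided 5% and 80% power (the power is not stated; 80% is inferred because it fits): 2 × (1.645 + 0.842)² × 20² / 9² = 61.1, rounded up to 62. It was not sized on the graded outcomes.

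**Assumptions.** The Protocol gives no grade distributions, so these are assumed. Control arm: 60/20/15/5% (four grades) and 35/15/25/15/7/3% (six levels). The other arm is shifted by a common OR of 2 at every cut. For four grades, the proportions at or above each cut move as follows:

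- 40%: odds 0.667 × 2 = 1.333, giving 57.1%
- 20%: odds 0.25 × 2 = 0.5, giving 33.3%
- 5%: odds 0.0526 × 2 = 0.105, giving 9.5%

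**Step 1: power on the full grade table** (simulation; repeat runs differ by up to about two points).

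| Outcome | Chi-square | Rank test | Loss |
|---|---|---|---|
| Four grades | 35% | 51% | 16 points |
| Six levels | 31% | 57% | 26 points |

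**Step 2: other assumed distributions** (20,000 trials each, 62 per arm, shift towards milder grades).

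| Outcome, assumed control distribution | OR | Chi-square | Rank test |
|---|---|---|---|
| Clavien-Dindo, 6-8 levels, 30% none, 2% death | 2 | 25-31% | 56% |
| same | 3 | 65-71% | 91% |
| Fistula none/A/B/C, 60/17/18/5% | 2 | 30% | 46% |
| Fistula none/B/C, 77/18/5% | 2 | 22% | 30% |
| Gastric emptying, 65/15/12/8% | 2 | 26% | 41% |
| Haemorrhage, 88/3/6/3% | 2 | 8% | 19% |

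**Step 3: theory check.** For 80% power at two-sided 5%, the required noncentrality is 7.85 on 1 df, 10.90 on 3 df and 12.83 on 5 df. The sample-size ratios are 10.90 / 7.85 = 1.39 for four grades and 12.83 / 7.85 = 1.63 for six. This agrees with the direction and rough size of Step 1.

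**Step 4: grades collapsed to two categories.** In the four-grade scenario at OR 2, with the rank test at 53% in the same run, chi-square has 51% power for any versus none, 39% at the next cut and 16% for the top grade alone: losses of 2, 14 and 37 points. With six levels the best cut gives 50% against 58%.

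**Step 5: sparse cells and error rate.** In the four-grade scenario the top grade has an expected count of 62 × (5% + 9.5%) / 2 = 4.5 per arm. At least one expected count fell below 5 in 59% of the four-grade tables and 97% of the six-level tables at OR 2. Type I error was nevertheless 4-5% in these scenarios. Across the distributions in Step 2 it was 3.1-4.6% for chi-square and 4.7-5.3% for the rank test. Sparseness makes chi-square somewhat conservative here; it does not create false positives.

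**Step 6: a shift that is not proportional.** If the overall rate stays the same but severity worsens, from 60/20/15/5% to 60/10/15/15%, chi-square has 46% power and the rank test 9%.

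**The case against.** The strongest reply is that nothing in the Protocol says the full grade table enters the test. The promised odds ratio fits a two-by-two comparison, and three of the four outcomes speak of a rate as well as severity. On that reading the loss can be nearly nil, as any versus none shows in Step 4. This stands, and it makes the Step 1 figures conditional on tabulating the full grades. It does not remove the point, because the cut-off is unstated and the loss depends heavily on it.

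A reader might infer from the small expected counts that chi-square is invalid in these tables and should give way to Fisher's exact test throughout. The error rates in Step 5 do not support that. A blanket switch would also hurt: for a 5% event rate at OR 2 with 62 per arm, Fisher's test has 8% power against 16% for chi-square, and its actual error at OR 1 is 1.1% against 4.6%.

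A reader might also infer that chi-square is the test least able to show cortisone to be worse. That is not shown: only a few tests were compared, mostly under the proportional shift that favours ranks, and Step 6 reverses the order.

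Finally, the CCI is itself built from Clavien-Dindo grades, so graded complication burden already enters the primary outcome. That stands and limits what is at stake.

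**Conclusion.** The point holds as a worthwhile improvement to the secondary analyses. The Protocol assigns a test that ignores order to four outcomes defined by ordered grades, and pairs it with an effect measure that a full grade table cannot supply. If full grades are compared and the effect is a roughly uniform shift of OR 2, about 16 points of power are lost with four grades and 26 with six levels. If grades are collapsed, the loss in the four-grade scenario runs from about 2 to 37 points with the cut. These sizes rest on assumed grade distributions.

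The non-inferiority conclusion on the CCI and the sample size of 124 are unaffected, and false-positive risk is not raised. Nor would the change make these outcomes well powered: at OR 2 the rank test in Step 2 reaches only 30-56%, and 19% for haemorrhage.

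**What to change.** In the Statistical analysis plan section:

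- Define one grade per patient for each graded outcome, namely the worst within 30 days.
- Compare these grades with a proportional-odds model, reporting the common OR with 95% CI, or with a Wilcoxon rank-sum test. The model supplies the odds ratio the section already promises.
- Keep chi-square with an OR for yes/no rates, and state every cut-off in advance, including one severe-grade comparison per outcome.
- Report the full grade table by arm.

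The last two items cover the known weakness of an ordinal test, which is insensitive when severity changes without a change in the overall rate. The cost is a few sentences and agreement on the worst-grade rule and the cut-offs before the data are seen. No new data are needed, because the grades are already collected.
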